### Treatment

The app offers an adaptation of scientifically proven techniques in the treatment of SAD based on Clark and Wells [4] and is intended for use as a mobile-based intervention. This intervention is designed to reduce the wait time for treatment and help therapists reduce the number of sessions while maintaining or increasing the effectiveness of treatment. The general idea is that using the app will facilitate the treatment process for both the patient and the therapist, as patients can practice the protocolized treatment steps in their environment and therapists can then incorporate these experiences into therapist-led change processes. The entire treatment program will last three months.

Clark and Wells’ model [4] aims to change the factors that maintain social anxiety. Treatment includes derivation of a model and behavioral experiments to test the effect of safety behaviors and self-focused attention, attention training, video feedback, further behavioral experiments, and cognitive restructuring. Based on this model and its German adaptations by Stangier et al. [28] and Hoyer and Härtling [29], the treatment includes the following modules:Module 1—Learning and Understanding: The goal of this module of the app is to provide the user with key information about SAD and to create an individualized model based on Clark and Wells’ approach. The information used to derive the model is based on patients’ self-reports of anxiety-provoking situations. The model is developed in a stepwise manner, prompted by feedback from the app.Module 2—Attention Training: The goal of the second module is to change self-focused attention. The training uses recorded audio exercises that train the ability to focus attention on external stimuli.Module 3—Behavioral experiments: This key module of the app consists of four phases. Each phase includes specific types of behavioral experiments, as well as various forms and questions for planning the experiments and recording the results and key findings.The first phase provides an experiment on how increasing or decreasing safety behaviors and self-focused attention affects anxiety. The experiment is supplemented by video feedback, in which patients are asked to record themselves in a simulated social situation (e.g., a presentation) and subsequently correct dysfunctional beliefs about their appearance or behavior.The second phase involves testing the dysfunctional beliefs that emerge in real social situations while simultaneously reducing safety behaviors and directing their attention outward.The third phase focuses on testing beliefs about the assumed negative impact of supposedly embarrassing behaviors on how they are evaluated by others (e.g., “If I pause during a presentation, I will appear awkward, and others will think I am an idiot”). Patients are instructed to explicitly demonstrate certain critical behaviors (e.g., pausing during a presentation) and to question the validity of their (possibly erroneous) beliefs.The fourth phase involves integrating behavioral experiments into daily life by continually testing SAD-related beliefs that interfere with personal goals.

In the therapist-guided app condition (TG-APP), use of the app is accompanied by eight therapist-guided video sessions. Based on the manual by Stangier et al. [28], the therapist assists patients in conducting behavioral experiments and provides a better understanding of the underlying processes. The goals of the sessions are as follows:First session: establishing a therapeutic alliance, exploring the symptoms and giving an introduction to the appSecond session: answering questions based on the individualized model of the app, deriving a second cognitive model by exploring safety behaviors and establishing motivation for changeThird session: performing a video recorded behavioral experiment to modify safety behaviors and self-focused attentionFourth session: analyzing the recorded video to test dysfunctional self-evaluation (video feedback)Fifth session: conducting a therapist-guided behavioral experiment testing a dysfunctional beliefSixth session: conducting a therapist-guided behavioral experiment deliberately showing critical behavior and testing the evaluation by othersSeventh session: motivating the patient to implement behavioral experiments into the everyday life and debriefing of previous behavioral experimentsEighth session: relapse prevention (summary of helpful techniques, pursuing personal goals, cognitive interventions for strengthening the self-esteem)

### Therapists

Therapists will be recruited mainly from the outpatient units of the Universities of Dresden and Frankfurt. All therapists must be either licensed psychotherapists or in advanced post-graduate CBT training (at least 1.5 years of training). Study-specific training will focus on how to use the app, how to conduct and analyze behavioral experiments, and how to use techniques of cognitive restructuring. Therapists are required to apply the TG-APP procedures with a pilot patient to gain experience and expertise in this particular form of blended therapy. All treatments will be supervised by psychotherapists with at least five years of clinical experience under their state licensure to ensure adherence to intervention protocols.

### Outcomes

#### Primary outcome measure

We defined the clinician-rated Liebowitz Social Anxiety Scale (LSAS) [21, 22], as the primary outcome measure, a measure widely considered the gold standard in controlled studies on SAD. The LSAS is designed as an interview to assess fear and avoidance in 24 different social situations (rated on a 4-point scale from “not at all” or “never” to “severe” or “most of the time”). The LSAS demonstrated good internal consistency (Cronbach’s *α* = 0.96), validity and treatment sensitivity [30].

#### Self-rating scales

As the secondary outcome measure for SAD, we use the Social Phobia Inventory (SPIN) [31]. The SPIN is a self-report questionnaire designed to assess the amount of discomfort in different situations during the last week. The total score can range between 0 and 68. Its psychometric properties are satisfactory [32, 33]. The Mini-SPIN [34], a short version with 3 items, is used as a screening instrument.

We also use the German version of the Social Cognitions Questionnaire (SCQ, German version: SPK) [35, 36], which lists 22 beliefs typically related to social anxiety (e.g., “People will see I’m nervous”) that are rated on two scales: the mean thought frequency, ranging from 1 (“thought never occurs”) to 5 (“thought always occurs”) and a mean belief rating, ranging from 0 (“I do not believe this thought”) to 100 (“I am completely convinced this thought is true”).

Symptoms of depression and general psychological distress will be assessed using the Beck Depression Inventory Fast Screen (BDI-FS) [37] and the 18-item version of the Brief Symptom Scale (BSI-18) [38]. The BDI-FS is the abbreviated version of the widely used Beck’s Depression Inventory (BDI-II) [39], which consists of 7 items, including for example “Sadness,” rated on a 4-point-scale. The questionnaire shows good reliability and validity ratings [40]. The BSI-18 is the short version of the original BSI [41], a questionnaire measuring general psychological distress rating items like “feelings of loneliness” on a scale from 0 (“not at all”) to 4 (“a lot”). The German version of the BSI-18 shows satisfactory internal consistency and validity [38]. Sensitivity to rejection in social situations are assessed with the Social Pain Questionnaire (SPQ-5) [42]. The questionnaire consists of 5 items (e.g., “If I have the feeling that a colleague pulls back from me, I feel rejected”) rating from 0 (“describes me perfectly”) to 4 (“not at all”). Initial psychometric properties show good reliability and validity [42].

To assess the quality of life, we will use specific domains of the WHO-QOL-BREF [43] that include the overall quality of life, as well as psychological quality, and quality of social relationships. The WHO-QOL-BREF asks for ratings on varying 5-point scales from 1 (e.g., “not at all” or “very dissatisfied”) to 5 (e.g., “completely” or “very satisfied”) for items like “How satisfied are you with your sleep?”. We excluded the domains of physical health and environment because they are not relevant to our study. The questionnaire shows good to excellent reliability and good validity [44].

To measure the amount of distress caused by the mental illness, we used the Pain and Disability Index (PDI) [45]. It consists of 7 different categories of life (like “Social Activity”), each of which is rated on a scale from 0 (“no disability”) to 10 (“total disability”). Reliability and validity seem adequate [46]. Additionally, the Anticipatory and Consummatory Interpersonal Pleasure Scale (ACIPS) [47] will be used to measure the pleasure patients experience in interpersonal situations with 17 items. It demonstrated good reliability and validity [47].

To assess if individual learning styles influence treatment effects, we included Kolb’s Learning Style Inventory (LSI) [48], where participants have to match different sentences (e.g., “when I learn…”) with four proposed items (e.g., “… I like to be active”) that are arranged on a scale from 1 (“describes me the worst”) to 4 (“describes me best”), so that each item for each sentence has a unique number from 1 to 4. It demonstrates satisfactory internal reliability and evidence for the suggested internal structure [49].

Treatment satisfaction will be measured by using the Client Satisfaction Questionnaire (CSQ) [50], which we adapted slightly to match the use of the app. This 8-item questionnaire uses questions like “How satisfied are you with the amount of help you received?“. It showed satisfying internal consistency and concurrent validity [51, 52]. Social anxiety and social approach behavior will be measured using a modified version of the Social Phobia Weekly Summary Scale (SPWSS) [53], which will be assessed by participants weekly (for the APP and the TG-APP condition) and at pre, mid, post and follow-up assessments (for all conditions). The SPWSS covers ratings of anxiety, avoidance, self-focused attention, anticipatory worry, post-event rumination, and social approach behavior. We added questions asking for feelings of pleasure and pursuit of personal goals and changed the scale to a 0–100 scale. The SPWSS is sensitive to treatment effects and has good internal consistency [53].

Finally, we will also assess negative side effects which are specific to patients with SAD. Drawing on the results of Boettcher et al. [19], we developed a brief (7-item) scale with items covering the negative side effects that were considered most relevant by a group of experts (see Additional file 1). The items are rated on a scale from 0 (“do not agree at all”) to 5 (“fully agree”). Please note that the descriptive list of possible side effects is preliminary and may be slightly revised after the pilot study. As the list contains an open item, responses to this item will be evaluated after the pilot study and inclusion of further side effects in the list is possible should they be mentioned frequently.

#### Clinician-rated measures

The interview will include the Structured Clinical Interview for DSM 5 (SCID-5) [54] conducted by clinician independent raters. Psychometric properties showed good reliability and specificity [55].

To screen for borderline personality disorder (BPD), we use a set of 5 questions suggested by Wongpakaran et al. [56] that screen for symptoms of BPD based on the DSM-V and a Rasch analysis. It showed good quality for assessing BPD [56]. If screening indicates that BPD may be present, we use the appropriate category of the SCID-5 to check for the other criteria of BPD.

We further use the Clinical Global Impression (CGI) [57] modified for patients with SAD. The CGI-Severity scale provides information about the current severity of social phobic symptoms which are rated on a 7-step scale from “normal” or “not ill at all” to “among the most severely ill patients” by a clinician. The CGI-Improvement scale is a 7-point scale rating the change in symptom severity from ‘improved by a lot’ to “a lot worse.” The use of the CGI, as a measure for symptom-specific improvement for patients with SAD, is supported by adequate psychometric properties [58] and its practicality.

Finally, the Quick Inventory of Depressive Symptomatology (QIDS-C) [59] will be applied, a 16-item rating instrument for the assessment of depressive symptoms by an independent interviewer, which showed acceptable internal consistency and treatment sensitivity [60]. Figure 2 gives an overview of the measures and assessments used in this study.

**Fig. 2 Fig2:**
[figure not shown]
Schedule of enrolment, allocation, interventions, and assessments

### Statistical methods

#### Sample

All analyses will be conducted in the intent-to-treat (ITT) sample, including all participants that were randomized into one of the three groups.

#### Primary analysis

For our primary analysis, we plan to fit a linear mixed model with random intercepts for participants in the R package lme4 [61]. We take the *z*-standardized values of the Liebowitz Social Anxiety Scale (LSAS) as the outcome variable, and time and treatment condition as categorical predictors, for which we specify an interaction term. The estimated effects of the predictor variables indicate the change in LSAS from baseline at week 0, which we choose as the reference category, to post-treatment.

#### Secondary analyses

As secondary analyses, we will evaluate treatment effects (from baseline to post-treatment, as described in hypothesis 2a and from post-treatment to follow-up, as described in hypothesis 2c) on quality of life, as measured by the WHO-QOL-BREF, interpersonal pleasure, as measured by the ACIPS, further SAD-related symptoms, as measured by the SPIN and the CGI, social phobic cognitions, as measured by the SPK, symptoms of depression, as measured by the BDI-FS and the QIDS-C, general psychological distress, as measured by the BSI, and limitations in everyday life, as measured by the PDI. We will also assess adverse effects measured by the self-developed adverse effect scale. Moreover, we will compare posttreatment LSAS scores with scores at follow-up, as stated in hypothesis 1c, using the linear mixed model described earlier.

To control for moderating effects on decreases in social anxiety symptoms, as indicated in hypothesis 3, we include the scores of the individual learning style, as measured by Kolb’s LSI and experienced pain in social situations, as measured by the SPQ-5, as predictors in the model and specify three-way interactions with treatment conditions and time for all these factors. We will conduct a similar analysis to test whether social approach behavior measured by the SPWSS has a mediating effect on social anxiety symptoms, as we hypothesized in hypothesis 4. We will test all interactions by comparing the full to a reduced model without the respective interaction term via likelihood ratio tests (LRTs) [62] and remove all non-significant interactions from the final model.

To evaluate effects between two conditions at a given time, e.g., between the APP and TG-APP conditions at post-treatment, as indicated in hypothesis 1b and 2b, we will calculate the statistical significance of pairwise differences in LSAS based on the linear mixed model using the R package “emmeans” [63].

We will fit all measures as outcome variables in linear mixed models including the same predictors as in the primary analysis and add the average weekly time participants spent using the app and the number of behavioral experiments conducted as additional explanatory predictors.

Besides that, we will analyze and compare responder rates between the different treatment conditions at post-treatment using a chi-squared test. Response to treatment will be defined as a 29% score decrease of the clinician-rated LSAS from baseline to post-treatment according to Glischinski et al. [64].

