### Objectives

The main goal of the present study is to evaluate whether the use of the app-based intervention helps to decrease symptoms of social anxiety disorder and has positive effects on mental health. There will be two experimental treatment conditions: App-based CT (APP) and app-based CT plus 8 therapist-guided video-delivered therapy sessions (TG-APP). Both will be compared to a wait-list control group (WLC). The therapists will be trained in Cognitive Therapy based on the model of Clark and Wells [4], which has been proven to be effective in face-to-face therapy [5] and in ICBT [15]. In a randomized controlled trial (RCT), the following hypotheses will be tested:Hypothesis 1a: In the APP and TG-APP condition, SAD-related symptoms, as measured by the LSAS, will decrease significantly more from baseline to post-treatment than in the WLC condition.Hypothesis 1b: The TG-APP condition results in a significantly greater reduction in SAD-related symptoms, as measured by the LSAS, than the APP and the WLC conditions, from baseline to post-treatment.Hypothesis 1c: In the APP and the TG-APP condition, there will be no significant deterioration of SAD-related symptoms, as measured by the LSAS, from post-treatment to follow-up.Hypothesis 2a: In the APP and TG-APP conditions, significant improvements in secondary outcome variables, including social phobic cognitions, depression symptoms, general psychological distress, psychological impairment, quality of life, and interpersonal pleasure, are achieved from baseline to post-treatment compared to the WLC condition.Hypothesis 2b: In the TG-APP condition, improvements in secondary outcome variables from baseline to post-treatment will be significantly larger than in the APP condition.Hypothesis 2c: In the APP and TG-APP condition, there will be no significant deterioration in secondary outcome variables from post-treatment to follow-up.Hypothesis 3: Individual learning styles contribute significantly to predicting success in both treatment conditions.Hypothesis 4: The increase in social approach behavior will mediate the effect of the TG-APP versus APP condition.

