### Allocation and randomization

Randomization is performed using a randomization list in which, based on 165 randomly generated numbers sorted by size, each of the available options is assigned according to the planned sample size (WLC = 43, APP = 61, TG-APP = 61). The list is then sorted by sequential number. A study coordinator who is not involved in the diagnosis or treatment process will enter the subjects into the randomization list according to the order of inclusion. The result is communicated to the patients via email and remains hidden from the clinical evaluators. The email to the participant contains the result and, if the person belongs to one of the two intervention groups, all the necessary information to use the app.

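### Hypothesis 4 is about mediation, but on the natural reading the plan tests it with a moderator interaction, which by itself cannot support or refute it

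*Protocol article*

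**What the plan says.** The Objectives section of the protocol article states hypothesis 4 as mediation between the two active arms: "The increase in social approach behavior will mediate the effect of the TG-APP versus APP condition".

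The Secondary analyses section first describes the model for hypothesis 3. Its purpose is given as "To control for moderating effects on decreases in social anxiety symptoms, as indicated in hypothesis 3". Learning style and social pain enter the LSAS mixed model as predictors, and the authors "specify three-way interactions with treatment conditions and time for all these factors". The next sentence covers hypothesis 4: "We will conduct a similar analysis to test whether social approach behavior measured by the SPWSS has a mediating effect on social anxiety symptoms". The decision rule follows directly: "We will test all interactions by comparing the full to a reduced model without the respective interaction term via likelihood ratio tests", after which the authors will "remove all non-significant interactions from the final model".

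The Self-rating scales section says of the SPWSS, which carries the social approach rating, "which will be assessed by participants weekly (for the APP and the TG-APP condition) and at pre, mid, post and follow-up assessments". The allocation is "WLC = 43, APP = 61, TG-APP = 61".

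**The concern.** Mediation of TG-APP versus APP requires two things. TG-APP must raise social approach relative to APP (path a), and social approach must predict LSAS improvement within arm (path b). The effect carried through the mediator is the product a × b.

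The only test described around the hypothesis 4 sentence is of an interaction. It asks whether the relation between social approach and LSAS change differs by condition, which is moderation. If the mediator works equally well in both arms, the interaction is zero however strong the mediation, and the plan would then drop the term. If the slopes differ but the arms do not differ in social approach, the interaction can be significant with nothing mediated.

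At stake is one numbered hypothesis. It bears on the mechanism put forward in the Discussion, that therapist contact helps patients overcome avoidance and engage in behavioral experiments.

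**Working it through.** The documents give no figure for hypothesis 4, so there is none to reproduce. The check is algebra followed by simulation.

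**Inputs from the protocol article.** 61 per arm in APP and TG-APP (Allocation and randomization). Expected dropout of 30% in APP and 20% in TG-APP, and dropout-reduced effects of 0.35 and 0.64 (Design and sample size).

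**Assumed inputs.** All path values and slope differences, and unit residual variances for mediator and outcome.

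**Model in change-score form.** Let G = 1 for TG-APP and 0 for APP, M = change in social approach, Y = change in LSAS:

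- M = i₁ + aG + u
- Y = i₂ + c′G + bM + hGM + e

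In this form, social approach × condition × time becomes the GM term, so the planned test is of h = 0.

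- With h = 0, the indirect effect is a × b. The planned test then rejects at its nominal 5%, whatever a and b are.
- With a = 0, the indirect effect is zero whatever h is. The planned test rejects more often as h grows.

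The planned test and hypothesis 4 therefore concern different parameters.

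**Simulation.** Two-sided 0.05, 61 versus 61, 3,000 runs per setting. The interaction likelihood ratio test is compared with a Monte Carlo 95% interval for a × b.

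| Assumed truth | Interaction test rejects | Indirect-effect test rejects |
|---|---|---|
| Full mediation, a = 0.6, b = −0.5, h = 0 | 5.4% | 91.2% |
| Stronger mediation, a = 0.8, b = −0.6, h = 0 | 5.2% | 99.0% |
| No mediation, a = 0, slopes 0 vs −0.6, direct effect 0.64 − 0.35 = 0.29 | 89.6% | 4.1% |
| Nothing present | 5.3% | 0.2% |

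**Sensitivity of the false-positive side.** With a = 0, the interaction test rejects in about 36% of trials at a slope difference of 0.3. At 0.6 the figure is 89% to 91% across separate runs.

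**Sensitivity to coding.** The plan does not say how SPWSS enters the model. A random-intercept mixed model with the protocol's variances (0.5 and 0.5) was run with SPWSS as time-varying, baseline-only and change score, with two arms and with three. Under full mediation with equal slopes the interaction test rejected in 5.1% to 5.9% in all six versions. With no mediation and differing slopes it rejected in 33% to 86%, depending on coding.

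**Power of the replacement test.** With the protocol's own dropout, about 61 × 0.7 = 43 and 61 × 0.8 = 49 are observed. Power at a = 0.6, b = −0.5 then falls from about 91% to about 80%. At a = 0.4 it is about 59% with complete data and about 48% with that dropout.

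**The case against.** The strongest reply is that the article never writes out the model for social approach. It says only that the analysis will be similar, and a condensed article may leave the indirect-effect estimator and interval to an analysis plan that is not shown. This stands in part: the three-way reading is the natural one, not a certainty, and missing estimator detail would be no finding. But the text does name a kind of analysis, and the sentences on either side describe only interactions and their likelihood ratio tests. An analysis plan that followed this wording would inherit the mismatch.

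A second reply is that both paths may be present in pieces. The section closes by saying that all measures will be fitted as outcomes, which could supply path a. SPWSS as a predictor of LSAS with arm in the model could supply path b. However, SPWSS is not among the secondary outcomes named in that section, and no rule uses either path to decide hypothesis 4. A treatment × mediator term can belong in a mediation model, but testing that term alone does not test mediation.

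A reader might also infer that the plan would reject hypothesis 4 whenever it is true and accept it whenever it is false. The documents do not support that. The first half holds when slopes are equal across arms, the second only when slopes differ without an arm effect on social approach. The documents give no path values or slopes.

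**Conclusion.** The point holds as a mismatch between hypothesis and stated method: a mediation hypothesis is assigned, on the natural reading, a moderation test. When mediation is real and slopes are equal, that test has no power beyond its 5% error rate, under every coding tried. When slopes differ without mediation it can be significant, in about 36% to 91% of trials for assumed slope differences of 0.3 to 0.6 with complete data in 61 per arm. By itself it can neither support nor refute hypothesis 4.

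The 5% follows from the algebra. The other rates, including all power figures for an indirect-effect test, rest on assumed values.

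This should be fixed, but it is not critical. Hypothesis 4 is secondary and mechanistic. The primary analysis, sample size, randomization and data collection are unaffected.

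**What to change.** In Secondary analyses, replace the reference to a similar analysis with wording to this effect:

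- Hypothesis 4 is tested by the indirect effect of TG-APP versus APP on post-treatment LSAS through change in SPWSS social approach.
- Two models supply it: the effect of arm on the mediator, and the effect of the mediator on LSAS given arm, adjusted for baseline LSAS and baseline SPWSS.
- The indirect effect is reported with a bootstrap or Monte Carlo 95% confidence interval.
- The mediator is SPWSS measured before the post-treatment LSAS, from the weekly or mid-treatment assessments, with the time point or summary fixed in advance by the trial team.
- The assumption of no unmeasured mediator–outcome confounding is stated.

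The time point needs thought. If the eight sessions were spread evenly over twelve weeks (an assumption), one would fall every 12 / 8 = 1.5 weeks. Sessions five and six, which hold the therapist-guided belief-testing experiments, would then come around or after week 6, and a week-6 mediator could miss much of the proposed mechanism. The weekly ratings allow a later summary. The text should also say how dropout is handled in this analysis.

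The cost is wording only: the weekly and mid-treatment SPWSS are already planned in both active arms.

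### Hypothesis 2b concerns secondary outcomes, but the statistical methods tie it to a TG-APP vs APP contrast on the LSAS, the primary outcome

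*Protocol article*

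**What the plan says.** All references are to the Protocol article.

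- **Objectives.** Hypothesis 2b reads: "In the TG-APP condition, improvements in secondary outcome variables from baseline to post-treatment will be significantly larger than in the APP condition". Hypothesis 2a describes the secondary outcome variables as "including social phobic cognitions, depression symptoms, general psychological distress, psychological impairment, quality of life, and interpersonal pleasure". The LSAS is not in that list.
- **Primary outcome measure.** "We defined the clinician-rated Liebowitz Social Anxiety Scale (LSAS) [21, 22], as the primary outcome measure".
- **Secondary analyses, first paragraph.** Treatment effects will be evaluated on nine instruments: WHO-QOL-BREF, ACIPS, SPIN, CGI, SPK, BDI-FS, QIDS-C, BSI-18 and PDI. The comparisons are described as "from baseline to post-treatment, as described in hypothesis 2a and from post-treatment to follow-up, as described in hypothesis 2c". Hypothesis 2b is not mentioned.
- **Secondary analyses, paragraph on pairwise comparisons.** For contrasts between two conditions, with APP vs TG-APP at post-treatment as the example: "as indicated in hypothesis 1b and 2b, we will calculate the statistical significance of pairwise differences in LSAS based on the linear mixed model", using emmeans.
- **Secondary analyses, last paragraph.** "We will fit all measures as outcome variables in linear mixed models including the same predictors as in the primary analysis". Each participant's weekly app-use time and count of behavioral experiments are then added as further predictors.

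**The concern.** A hypothesis about depression, distress, impairment, quality of life and similar outcomes has been given a test whose null is that the two app conditions do not differ on the LSAS. That test can support or reject hypothesis 1b. It carries no direct information on whether therapist guidance improves any secondary outcome.

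What is at stake is the reference against which 2b will later be judged. Anyone checking the final report against the article finds one rule for 2b, on the wrong outcome. The fallback is a set of models with no assigned contrast and with predictors that change what a contrast would mean. The choice between adjusted and unadjusted secondary contrasts would then be open when the results are known.

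**Working it through.** No sample size, power or alpha enters this point, so there is no figure to reproduce. The check sets each hypothesis beside the analysis linked to it.

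| Hypothesis | Comparison and outcome (Objectives) | Analysis that names it (Secondary analyses) |
|---|---|---|
| 1b | TG-APP vs APP and WLC, LSAS, baseline to post | Pairwise differences in LSAS |
| 2a | APP and TG-APP vs WLC, secondary outcomes, baseline to post | Treatment effects on the nine secondary instruments |
| 2b | TG-APP vs APP, secondary outcomes, baseline to post | Pairwise differences in LSAS |
| 2c | APP and TG-APP, secondary outcomes, post to follow-up | Treatment effects on the nine secondary instruments |

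**Step 1: outcome.** Rows 1b and 2b have different outcomes in the second column and the same test in the third. For 1b the test fits. For 2b it does not.

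**Step 2: is 2b assigned anywhere else?** It is not. The paragraph listing the secondary instruments names 2a and 2c. The last paragraph of the section names no hypothesis and no pairwise contrast.

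**Step 3: would the models in the last paragraph give the right quantity?** With the primary-analysis predictors alone (condition, time and their interaction), the quantity that 2b describes is

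(TG-APP post mean − TG-APP baseline mean) − (APP post mean − APP baseline mean)

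for each secondary outcome. The models as specified also contain app-use time and number of behavioral experiments. Both are measured after randomization. The Discussion expects therapist contact to keep patients from doing too few behavioral experiments, which it regards as an important active component of the therapy. The experiment count is therefore one route by which TG-APP is expected to work.

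- The pairwise difference at post-treatment, which is the contrast that the emmeans sentence describes, becomes a difference at equal app use and equal numbers of experiments. It is no longer the overall difference.
- If the usage predictors also interact with time, the contrast in change becomes conditional in the same way.
- If they enter only as person-level main effects and the data are complete, the contrast in change is unaffected. The article does not say which form is meant.

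So a TG-APP vs APP contrast from these models is not, in general, the effect that 2b states. Whether it is depends on a choice that the article leaves open.

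**The case against.** The best defence is that one sentence is being read apart from its section. The parenthesis naming 2a and 2c marks time windows and does not say that only those hypotheses are tested on the secondary instruments. Hypothesis 2b uses the same baseline-to-post window as 2a. The models for all measures include the three-level condition factor and so contain the TG-APP vs APP comparison. The emmeans sentence introduces its contrast as an example of a general procedure. On this reading, the procedure serves 1b on the LSAS and 2b on the secondary measures, and the restriction to LSAS is a slip. Details of contrasts by endpoint are also often left to a full analysis plan.

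Much of this stands. A reader might infer that 2b will be decided on the LSAS alone and that the secondary outcomes will not be analysed. The article does not support that, because it plans to evaluate and model every listed measure. A reader might also try to attach false-positive or missed-effect rates to the mismatch. Such rates would only be the power of ordinary two-sample tests under effects the reader had assumed, and would not show that the plan will be carried out that way.

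Two parts do not stand. First, this is not an omission left to a fuller document: the article names the hypothesis, the contrast, the software and the outcome, and the outcome is wrong. Second, the models for all measures do not correct it, because they assign nothing to 2b and include the usage predictors.

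**Conclusion.** The point holds as an error in the stated analysis rule. Hypothesis 2b is assigned to a contrast on the primary outcome, which duplicates the test for 1b, and no other passage assigns it a contrast on the outcomes it concerns.

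The weight is modest. One secondary hypothesis is affected. The primary analysis, the sample size and the data collection are unchanged. The conclusion rests on the wording alone and needs no numerical assumption. The further statement, that the existing secondary models would not in general yield the 2b effect, rests on the usage variables arising after randomization and on the article's own expectation that therapist guidance increases behavioral experimentation.

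**What to change.** In Secondary analyses:

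1. Limit the pairwise LSAS contrast to hypothesis 1b.
2. For hypothesis 2b, state that the TG-APP vs APP contrast in change from baseline to post-treatment will be obtained with emmeans from each secondary outcome's own condition × time mixed model, without app-use time or number of behavioral experiments. Name the outcomes: WHO-QOL-BREF, ACIPS, SPIN, CGI, SPK, BDI-FS, QIDS-C, BSI-18 and PDI. For the CGI, say which scale is meant, since the improvement scale is itself a rating of change.
3. Keep the models with the usage predictors as separate explanatory analyses that do not decide 2b.

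The cost is a few sentences of wording. No new data, visits or participants are needed, and the unadjusted models use the same predictors as the primary analysis.
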